Benjet et al. (2023) [30] used a machine learning precision treatment modelling method [31] to develop an ITR. We propose adopting a similar approach,thereby, to our knowledge, making the current study the first application of this approach to a European university student sample. This provides an opportunity to examine if similar patterns of heterogeneity of treatment effects and similar ITRs emerge in a UK higher setting compared to those found in Latin American higher education [27, 30]. Following the precedent of Benjet et al. (2023) [30], we will assess an extensive set of potential predictors of individual differences in the effects of CBT, that is, potential prescriptive predictors [32], moving beyond prior research that only examined a small battery of predictors [33]. As such, we aim to test whether it is possible to generate a useful ITR for guided versus unguided i-CBT in the UK university context.

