### Objective

The primary objective is to examine the aggregate efficacy of guided transdiagnostic i-CBT relative to unguided i-CBT to reduce symptoms of depression and anxiety over a 3-month period in university students who report elevated depression and/or anxiety, as operationalized by caseness on well-established self-report measures. As noted above, we know from much previous research that the aggregate efficacy of guided i-CBT is likely to be significantly higher than that of unguided i-CBT. A secondary objective is to use machine learning methods to predict heterogeneity of treatment effects of unguided iCBT versus guided iCBT and develop ITRs to predict which students will respond as well as, or possibly even better than, to self-guided as to guided i-CBT.

We hypothesize that consistent with prior findings [17, 20, 24, 25, 27, 28], for university students with elevated depression and/or anxiety, the guided i-CBT will outperform unguided i-CBT in the aggregate in reducing symptoms of depression and anxiety across 3 months. We further hypothesize that a small subset of users will benefit at least as much from unguided as from guided i-CBT and that we will be able to identify this subset of students prior to randomization using machine learning methods [30]. Importantly, we also anticipate that some proportion of students will fail to improve meaningfully with either guided or self-guided i-CBT and that we will be able to identify this segment of the population with good accuracy using the same machine learning measures as those used to develop the ITR. If so, this information could be used to refer such students to more intensive care rather than requiring them first to fail as a course of i-CBT.

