### Sample size

The sample size for the efficacy question was calculated using the co-primary outcomes based on a minimum clinically important difference (MCID) at primary endpoint allowing for power at 0.80 and a two-sided alpha at 0.05 and using a Bonferroni correction for the two tests. The co-primary outcomes are symptoms of depression (PHQ-9) and anxiety (GAD-7) at 3 months follow-up. Based on previously established MCID for these measures (PHQ-9, MCID 2.59, SD = 5.4; GAD-7, MCID 4, SD = 5.07) [55, 56] and assuming 20% follow-up attrition, the calculated sample sizes are *n* = 129 per arm and *n* = 41 per arm respectively, with the larger of these (n = 129 per arm) the one required to satisfy the power requirements for both co-primary outcomes after the Bonferroni correction, i.e. a total sample of *n* = 258.

However, to power the study for the development of an ITR, we followed the recent recommendation arising from machine learning stimulations, which suggested that at a power of 0.80 based on a two-sided alpha of 0.05, a sample of at least 300 patients per arm is needed to develop an ITR that can detect a clinically meaningful difference in remission rates (between 5 and 10%) assuming a baseline remission rate from depression of 30% from both treatments aggregated [57]. As such, we increased the sample size to 300 participants per arm as the minimum to obtain stable estimates and generate a reliable ITR. This sample size gives a power of greater than 99% to compare the efficacy of guided versus unguided i-CBT.

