For the purposes of precision models, we will first explore which pre-treatment measures moderate the differential effects of treatment condition. Because individual predictors are usually weak and underpowered, our primary approach will be to use composite models that combine individual moderators to produce ITRs that can guide the selection of treatments most likely to be helpful for individual students. The approach will follow precedents established for developing precision treatment models via cross-validated machine learning methods as used in similar studies [30, 59–61]. Such machine learning methods for estimating heterogeneity of treatment effects include extensions of the generalized random forest algorithm [62–64] and of the Super Learner algorithm [65, 66], an ensemble machine learning approach. We will use the generalized random forest algorithm [62–64], with the option to add machine learning approaches (including ensemble approaches) as necessary, to develop a model that best predicts the relative effectiveness of alternative interventions. The machine learning approach has been validated for developing effective composite models, e.g. developing preliminary ITR with *n* = 150 [57, 61] and has the advantages of avoiding the need to specify main effects correctly and allowing the data‐driven estimation of nonlinear and higher‐order complex interactions across predictors. The value of guided and unguided iCBT at the individual level will be quantified using a counterfactual approach estimating the attained improvement of the mean outcome under a treatment selection scheme that always selects the treatment option with the best predicted outcome compared to the mean outcome under balanced randomization, generating a difference score or a personalized advantage index [67].

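### The treatment rule is valued only against balanced randomization, which mixes the average advantage of guidance with any benefit of tailoring

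*Protocol article*

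**What the plan says.** In the protocol article, the precision-model paragraph of the section Statistical analysis plan values guided and unguided i-CBT at the individual level through a counterfactual comparison. The policy under study gives each student the option with the "best predicted outcome compared to the mean outcome under balanced randomization". No other passage offers a single-arm policy as a reference for the rule.

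The section Objective states the expected average effect twice: "we know from much previous research that the aggregate efficacy of guided i-CBT is likely to be significantly higher than that of unguided i-CBT", and, as a hypothesis, "the guided i-CBT will outperform unguided i-CBT in the aggregate in reducing symptoms of depression and anxiety across 3 months". It then gives the secondary aim, to "develop ITRs to predict which students will respond as well as, or possibly even better than, to self-guided as to guided i-CBT", and expects the subset who do at least as well unguided to be small. The section Background sets the broader goal: "we aim to test whether it is possible to generate a useful ITR for guided versus unguided i-CBT". Allocation is 1:1 (section Randomization, intervention delivery, and masking), so the balanced reference weights each arm by one half.

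**The concern.** Balanced randomization gives half the students the arm that the plan expects to be worse. Any policy that moves most students to the other arm beats it, whether or not the choice depends on a predictor. The index therefore answers whether the rule is better than a coin toss. The stated question is whether tailoring by student is useful.

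Held-out estimation does not remove the problem, because it comes from the comparator and not from overfitting. The index also hides a loss. A noisy rule that sends some students to the worse arm for no gain can still show a positive value.

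The rule is the reason the sample rose from 258 in total to at least 300 per arm (section Sample size), and the Discussion presents it as a step towards definitive trials. A value that is mostly average effect would be a weak basis for that step.

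**Working it through.** **Plan figures.** The article gives no figure for the value of the rule. The nearest is the power above 99% for guided against unguided with 300 per arm. With a PHQ-9 difference of 2.59, SD 5.4 and two-sided alpha 0.025 (0.05 with Bonferroni for two tests), power is 0.9999, or 0.9987 with 240 per arm after 20% attrition. The claim reproduces, and the same difference and SD are used below.

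**Identity.** Score outcomes so that higher is better, let V be the mean outcome under a policy, and let D = V(all guided) − V(all unguided). With weights of one half:

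V(balanced) = V(all guided) − D/2

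V(rule) − V(balanced) = D/2 + [V(rule) − V(all guided)]

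Only the bracket measures tailoring against guided care for all.

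**Constant effect.** If every student gains D from guidance and the rule sends a share p to guided care:

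- V(rule) − V(balanced) = pD − 0.5D = (p − 0.5)D, at most D/2
- V(rule) − V(all guided) = −(1 − p)D, never above zero

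**Size of D/2.**

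- PHQ-9 at the plan's difference: 2.59/2 = 1.295, about 1.30 points
- GAD-7 at the plan's difference: 4/2 = 2.0 points
- PHQ-9 at assumed standardised effects of 0.1, 0.2 and 0.3 (SD 5.4): 0.54/2 = 0.27, 1.08/2 = 0.54 and 1.62/2 = 0.81 points
- D = 0: zero

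**Simulation without heterogeneity.** There were 600 participants, 20 predictors, a 10-fold cross-validated rule with one ridge model per arm, and 400 trials per row. Values are PHQ-9 points.

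| D | Mean share p to guided | (p − 0.5)D | Estimated gain v balanced | Estimated gain v all guided |
|---|---|---|---|---|
| 1.08 | 0.741 | 0.26 | +0.27 | −0.27 |
| 1.62 | 0.830 | 0.53 | +0.54 | −0.26 |
| 2.59 | 0.933 | 1.12 | +1.12 | −0.17 |

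The estimated gain was positive against balanced randomization in 79%, 96% and 99.8% of trials. Against all guided it was positive in 12%, 6% and 6%.

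**The index cannot separate the two sources.** When D = 0 and the individual effect has a true SD of 2 points, the same simulation gives +0.55 against balanced and +0.56 against all guided. So a gain of about 0.54 can come from real tailoring with no average effect, or from D = 1.62 with no heterogeneity at all. At D = 2.59 the index is 1.12 without heterogeneity and 1.25 with it.

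**Dependence on the learner.** Two further runs with 576 participants (720 less 20%) and 40 predictors gave +0.20 and +0.37 against balanced at D = 1.08, and −0.32 and −0.18 against all guided. The sign pattern is stable but the sizes are not. In each run the two gains differ by about D/2 = 0.54 (0.20 + 0.32 = 0.52; 0.37 + 0.18 = 0.55), as the identity requires.

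**The case against.** The algebra is hard to dispute. The serious objections concern how far it reaches.

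- **No test is planned on this value.** The article says only that the value will be quantified. A reader might infer that the trial will often declare a useful rule falsely. A 5% test added in the simulations does flag a gain over balanced randomization in 15% to 43% of null trials at a standardised effect of 0.2, and in 95% to 100% at 0.48. But that test is not in the plan and the rates move with the learner, so they are illustrative only. This objection stands.
- **The 5 to 10% remission range.** A reader might infer that an untailored rule already reaches the plan's meaningful gain, since assumed arms at 35% and 25% average 30% and give 0.35 − 0.30 = 5 points. The section Sample size states its range "assuming a baseline remission rate from depression of 30% from both treatments aggregated" but does not say which reference policy it applies to. The match cannot be claimed.
- **The aim is wider than mean outcome.** The Objective also seeks students who do as well unguided, for reasons of scale. A rule that moves some students to unguided care without loss would only tie with all guided, yet would be a success. This stands and shapes the fix.
- **Other outputs address heterogeneity.** Moderator exploration, the generalized random forest and the individual difference scores could show that little varies. A reader could also subtract D/2, with D taken from the primary analysis. This reduces the risk of misreading but leaves the stated reference unchanged. Subtraction recovers a point estimate without its uncertainty.
- **The full analysis plan may add a contrast.** It may, but the article fixes a comparator that does not answer its own question.

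**Conclusion.** The concern holds as a fault in the stated comparator. With D > 0, as the article expects, the index contains a D/2 term that owes nothing to tailoring: 1.30 PHQ-9 points at the planned difference and 0.54 at an assumed effect of 0.2. A fitted rule with no heterogeneity behind it shows (p − 0.5)D, which is less than D/2 whenever it sends anyone to unguided care. A reader might infer that exactly half the average effect is always credited to the rule; that is only the limiting case.

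The identity needs only the 1:1 weights. The sizes rest on the true D, which is unknown, and the problem disappears if D is zero. The co-primary comparison, randomization and data collection are unaffected. The severity is should-fix, for a secondary objective.

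**What to change.** In the precision-model paragraph of the section Statistical analysis plan, replace the balanced-randomization reference with wording such as:

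> The cross-validated mean outcome under the rule will be compared, with confidence intervals, with the mean outcome if all students received guided i-CBT and if all received unguided i-CBT. The comparison with balanced randomization will be reported descriptively.

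Then state two separate readings:

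1. Tailoring is said to improve outcomes only if the rule beats the better single-arm policy.
2. For the aim of finding students who do as well unguided, report the share that the rule assigns to unguided care, with the estimated loss or gain against all guided and its interval. Superiority over all guided is not required here.

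The cost is a wording change and two extra contrasts on the same data. The stated benefit of the rule will probably be smaller. The change should be made before the unblinded analysis, so that the choice of reference cannot look driven by the data.

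### The treatment rule is valued only against 50:50 allocation, so its reported value includes half the average guided-versus-unguided effect and cannot by itself show that personalization helps

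*Protocol article*

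**What the plan says.** In the protocol article, the precision-model paragraph of the Statistical analysis plan section defines both the rule and its yardstick. The rule is "a treatment selection scheme that always selects the treatment option with the best predicted outcome". Its value is the improvement "compared to the mean outcome under balanced randomization, generating a difference score or a personalized advantage index". Neither that paragraph nor the secondary-analysis text after it names another comparator policy.

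The Objective section gives the expected direction of the average effect: "the aggregate efficacy of guided i-CBT is likely to be significantly higher than that of unguided i-CBT". This is also the trial hypothesis: "the guided i-CBT will outperform unguided i-CBT in the aggregate in reducing symptoms of depression and anxiety across 3 months". The aim for the rule is to predict "which students will respond as well as, or possibly even better than, to self-guided as to guided i-CBT", and the authors expect that "a small subset of users will benefit at least as much from unguided as from guided i-CBT".

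**The concern.** A treatment rule is worth having if it does better than the best policy that ignores patient characteristics. Half-and-half allocation is the best such policy only when the arms are equal on average, and the authors expect them to differ. The stated measure therefore adds the average effect to whatever personalization contributes and does not separate the two.

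The rule being valued also does not quite match the question asked. It sends a student to unguided only when unguided is predicted to be better. A student predicted to gain almost nothing from guidance still goes to guided. Yet the Background and Discussion sections say that finding students who do equally well without a practitioner is what makes the work useful for scaling services.

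The rule is a secondary objective, but it raised the required sample from 258 in total to at least 600 (300 per arm), and it is meant to inform how universities allocate support.

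**Working it through.** **Inputs.** From the Sample size section: PHQ-9 difference 2.59, SD 5.4; GAD-7 difference 4, SD 5.07; two-sided alpha 0.05 with Bonferroni for two tests (0.025 each); 20% attrition; 300 per arm. From Study design: 1:1 allocation. Below, D is guided's average advantage, V is the mean benefit under a policy, and higher V is better.

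**1. The plan's own figure.** The article gives no number for the rule's value. It does state power above 99% for the average comparison at 300 per arm. With power = Φ(D / (SD·√(2/n)) − 2.241):
- PHQ-9, n = 300: 2.59 / (5.4 × 0.0816) = 5.87; 5.87 − 2.24 = 3.63; power 0.9999.
- PHQ-9, n = 240 after 20% loss: 2.59 / (5.4 × 0.0913) = 5.25; 5.25 − 2.24 = 3.01; power 0.9987.
- GAD-7: above 0.9999 in both cases.

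The statement reproduces. If D is near these values, the trial will almost certainly detect it as an average effect.

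**2. What the benchmark adds.** V(50:50) is the mean of V(all guided) and V(all unguided), which is V(all guided) − D/2. Hence, for any rule,

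V(rule) − V(50:50) = D/2 + [V(rule) − V(all guided)].

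When guided is the better arm, only the bracket measures personalization. For the rule that sends everyone to guided the bracket is 0, and the stated measure gives:
- PHQ-9: 2.59 / 2 = 1.295 points
- GAD-7: 4 / 2 = 2.0 points
- assumed smaller effects: D = 1.0 gives 0.5; D = 1.5 gives 0.75

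A rule that is worse than all-guided still scores above zero as long as its shortfall is below D/2.

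**3. A fitted rule with no heterogeneity.** Two simulations used cross-validated linear learners in place of the generalized random forest and gave every student the same treatment effect. The significance rates refer to a nominal test that the article does not specify.

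| Setting | D | Gain over 50:50 | Nominally significant | Gain over all-guided |
|---|---|---|---|---|
| 10 noise covariates, 300 per arm | 2.59 | +1.16 | 99% | −0.13 |
| same, 240 per arm | 2.59 | +1.13 | 97% | −0.18 |
| ridge, 40 predictors, 288 per arm | 2.59 | +0.97 | 96% | −0.34 |

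The gain over all-guided was never significant. The first row can be checked by hand. About 95% of students went to guided, so the expected gain is (0.95 − 0.5) × 2.59 = 1.17 over 50:50, and −0.05 × 2.59 = −0.13 against all-guided.

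With smaller assumed effects the nominal rate falls. In the first setting it was 60% at D = 1.5 (mean gain +0.50), 27% at D = 1.0 (+0.25) and 6% at D = 0 (0.00). With ridge it was 41% at D = 1.62 and 17% at D = 1.08.

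**4. With real heterogeneity.** Assume normally distributed individual effects with mean 2.59 and SD 2, so z = 2.59/2 = 1.295. A perfect rule gains 2 × [φ(1.295) − 1.295 × (1 − Φ(1.295))] ≈ 2 × (0.1725 − 1.295 × 0.0977) ≈ 0.09 over all-guided. Over 50:50 it gains 1.295 + 0.09 ≈ 1.39. The average effect is then 1.295 / 1.39, or about 93%, of the stated value.

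**The case against.** Several defences have weight.

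- *No success criterion is attached.* The article says the value will be quantified; it sets no test or threshold. A reader might infer that the trial would declare a useful rule whenever guided wins. The text does not support that, and the significance rates above belong to a test it never states. This stands.
- *Individual scores are produced as well.* A reader might infer that the analysis cannot find students who do equally well on unguided. The same sentence yields an individual difference score, and the section also plans moderator exploration and a heterogeneity-oriented forest. Those scores can show who lies near zero. What remains is that the valued rule does not use them that way.
- *The missing contrast can be recovered.* Subtracting D/2 from the stated measure gives a point estimate against all-guided, and D is estimated in the primary analysis. This is true on a common outcome and analysis set, but it gives no confidence interval and relies on the reader to do it.
- *Balanced randomization is defensible.* It is the trial's own allocation, and the Discussion names random allocation or usual practice as comparators for later trials. Guided for all is not the evident status quo either; the article says universities often offer i-CBT unguided. This supports reporting several benchmarks, not one.
- *The differences used for sizing are not predictions.* They are minimum important differences, and the Background describes effects of digital CBT in students as small on average. This stands and limits the size of the problem.
- *Superiority over the best arm is the wrong test for scalability.* A rule that correctly sends equal-benefit students to unguided scores about zero against all-guided, or slightly below if it accepts a margin. This stands and shapes the fix.

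Cross-validation is no answer. It removes overfitting, but the average effect is real out of sample.

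**Conclusion.** The point holds in a limited form. The only stated benchmark puts D/2 of main effect into the rule's reported value: 1.295 PHQ-9 or 2.0 GAD-7 points if D equals the differences used for sizing, and proportionately less otherwise. This is exact algebra for any D above zero, and the authors expect D to be above zero. A positive value is therefore not evidence of benefit from personalization and could be reported for a rule that does no better than guided for all.

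How often such a value would reach nominal significance is not fixed by the documents. It depends on D and on the learner: near certain at 2.59 points, roughly 17% to 27% at about 1 point in the simulations.

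The mismatch between a best-arm rule and an equal-benefit objective is real but partial, because the individual scores are there to be used. The separate statistical analysis plan is not shown and may add a comparator. The article as written fixes only this one. It should be fixed; the primary comparison, randomization and data collection are unaffected.

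**What to change.** In the precision-model paragraph of the Statistical analysis plan section, before unblinding:

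1. Add the out-of-fold contrast of the rule with each single-arm policy, all-guided and all-unguided, with confidence intervals. Rest any claim that personalization improves outcomes on the contrast with the better single arm. Keep the comparison with balanced randomization as a descriptive figure.
2. For the equal-benefit objective, pre-specify a margin on the predicted guided-minus-unguided benefit. Report the share of students below it and the out-of-fold guided-versus-unguided difference in that group. Judge that difference for non-inferiority against the margin, not by superiority over all-guided. The trial team must choose and justify the margin.

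The cost is wording and a few extra contrasts from the same out-of-fold predictions. No new data are needed. The reported gain from the rule will be smaller.

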### Organization, quality assurance and data management

Research data will be automatically collected in a pseudonymized manner through an electronic data capture system licenced/programmed by Exeter Clinical Trials Unit (ExeCTU). In the first instance, all participants will be directed to the electronic data capture system to provide their data. Participants who respond to follow-ups by telephone will have their primary outcome data entered into the system by a site researcher, and this variation in data collection method will be recorded in the EDC. All data will be kept securely and confidentially and only accessed by specified researchers at the University of Exeter. The central data-management team will use de-identified backups for the monitoring of the overall progress and data quality, following a detailed study-specific Data Management Plan, which is available on request. Ultimately, a comprehensive de-identified dataset will be produced that includes all outcome data.

